### 3.4. Selection Criteria

To pre-select participants candidates to sampling, a standardized questionnaire regarding general health will be applied, including the presence of concomitant systemic diseases, daily intake of prescribed medication, as well as a *Self-reported assessment of Periodontitis*, self-perception of gingivitis, dental care, and oral hygiene habits (38).

#### 3.4.1. Inclusion Criteria

Women and men between 20 and 50 years old.People who live in Mexico City.People without hypertension.People who do not take medications that affect blood pressure.People without chronic infections, inflammatory, immune disorders, or other systemic conditions such as diabetes.People who agree to participate in the study and sign the informed consent.

#### 3.4.2. Exclusion Criteria

People diagnosed with cancer with an effect on survival.Pregnancy or lactation.People with cognitive and mental disabilities.Edentulous people.People with dental implants.People who are undergoing systematic and regular periodontal treatment.People with forms of refractory or progressive periodontal rupture, periodontitis in a rapid rate of progression, necrotizing periodontal diseases or periodontal abscess that require regular taking of antibiotics.

#### 3.4.3. Elimination Criteria

People who develop hypertension and initiate and/or maintain regular and active antihypertensive therapy.People who develop systemic and uncontrolled diseases that may interfere with the severity of periodontitis.People who initiate and maintain regular and active periodontal treatment during the study follow-up.People who develop some forms of periodontitis that require regular antibiotics.People who undergo dental procedures that involve implant placement.

### 3.5. Variables (Identification, Definition, and Measurement Scales)

#### 3.5.1. Definition of Variables

Dependent-variable of interest: Incidence of hypertension.Independent-variables of interest: Periodontal-related parameters and oral-related microbial profiles.Oral health covariates: Oral health related quality of life; diet changes; perception of need for dental treatment; xerostomia; use and functionality of removable dental prostheses; oral hygiene (presence of biofilm and dental calculus); number of natural teeth present; dental caries; root debris and gingival bleeding.

### 3.6. Dependent Variable

#### 3.6.1. Systemic Arterial Hypertension

Blood pressure assessment will be performed every 2 years in accordance with the *2020 International Society of Hypertension Global Hypertension Practice Guidelines* (39). Hypertension will be diagnosed when (1) a person's systolic blood pressure (SBP) in the office is ≥140 mm Hg and/or their diastolic blood pressure (DBP) is ≥90 mm Hg after at least 3 repeated examinations and (2) when a person's systolic blood pressure (SBP) at home (HBPM) is ≥135 mm Hg and/or their diastolic blood pressure (DBP) is ≥85 mm Hg. Classification values are charted below (39).

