### 2.2. Specific Goals

Specifically we will reach the above mentioned goals through the following steps:

Estimating the prevalence of periodontitis in people aged 20 years and older at baseline in the cohort under study.Identifying differences in the distribution of known cardiovascular risk factors (age, gender, weight, physical activity, smoking habit, and stress) and social determinants of health (education, occupation, and marital status), in individuals with and without periodontitis at the beginning of the study.Estimating and assessing the impact on the quality of life of individuals with varying degrees of periodontitis at the beginning of the study.Identifying differences in the perceived need for dental treatment and the use of dental services between individuals with and without periodontitis at the beginning of the study.Studying the association between the subgingival microbiome profiles and the periodontal health conditions or periodontitis at baseline.Identifying whether cardiovascular risk factors and social determinants of health are associated with the risk for periodontitis and with the 60-month incidence of arterial hypertension in participants of the study.Analyzing the distribution of xerostomia, the use and functionality of removable prostheses, the presence of root remains, the number of present natural teeth, the number of teeth with caries, as well as the oral hygiene habits in persons with and without periodontitis.Identifying if there is any association between the 60-month incidence of hypertension and the baseline salivary and subgingival microbiome and the baseline presence of periodontitis.Analyzing the relative abundance of microbial species profiles in the salivary and subgingival microbiome and its relationship with arterial hypertension within a 60-month follow-up.Contrasting the epidemiological evidence of the relationship between periodontitis and hypertension with the findings of the analysis of the subgingival periodontal microbiome.

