### 2.3. Hypotheses

The main hypotheses motivating the design of this project may be summarized as follows:

Individuals with periodontitis have an augmented risk of developing arterial hypertension than people without periodontitis, within a 60-month period controlling for: sex, age, smoking, and oral hygiene habits; as well as social determinants of health such as education, occupation, and marital status.The relative abundance of microbial species profiles in the subgingival periodontal microbiota of participants with and without periodontitis will be different.The relative abundance of microbial species profiles in the salivary and subgingival periodontal microbiota of participants that develop arterial hypertension will be different to that of the ones not developing HBP.

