#### 3.2.1. Participants and Recruitment

The study population is a sub-cohort of the participants in a cohort from the Mexico City metropolitan area (35). It is a prospective longitudinal study in which clinically healthy residents of Mexico City, between 20 and 50 years old are recruited to be evaluated every 2 years for a period of 10 years or until they develop hypertension. Anthropometric (weight, height and waist circumference), clinical and biochemical parameters (blood and urine laboratory tests with markers such as glucose, cholesterol, triglycerides, sodium and potassium, etc.), nutritional and lifestyle habits (physical activity, sleep quality, alcohol and tobacco consumption) and social determinants of health are assessed (Supplementary Material). All participants are measured periodically (every 2 years) by a battery of specific serum biomarkers of systemic inflammation. Participants will be contacted every 6 months via email or by telephone to assess their medical and dental history including treatment for hypertension and/or periodontitis, as well as any medication (including antibiotic treatment) used over the previous months (see Figure 1).

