##### 3.6.1.2. Blood Pressure Measurement Plan According to Office Blood Pressure Levels

Repeated examination and/or measuring BP levels at home will be performed as follows:

Participants with normal BP (<130/ <85), will be re-examined on at least one further office visit (1–2 week intervals).Participants with suspected high-normal BP (130–139 and 85–89), will have repeated office visits (2 at 1–4 week intervals) required and will be asked to monitor blood pressure for at least 5 (preferably 8) consecutive days at home (HBPM).Participants with suspected hypertension (≥140 and ≥90), repeated office visits (3 or 4 visits at 1–4 week intervals) for re-examination will be required. Also, they will be asked to monitor blood pressure for 8 consecutive days at home (HBPM). Those diagnosed with HBP during this period (see HBPM below) will be referred to the ambulatory blood pressure monitoring (ABPM) service at the INC-ICh.The diagnosis will be made on a single visit, if BP is ≥180/≥110 mm Hg on the first set of three measurements. Then the participant will be immediately scheduled for a clinic visit at the INC-ICh to receive appropriate treatment. The day of the diagnosis of hypertension will be considered the date of disease onset.

Participants who are diagnosed with HBP at another facility at any time during the study will be requested to immediately notify principal investigators. These participants will be asked to schedule a visit at the INC-ICh prior to starting any medical treatment, to confirm the diagnosis and to complete the “end of the study” visit. Also, participants who are diagnosed with HBP and initiate and maintain regular antihypertensive therapy (more than 2 weeks) will be eliminated, according to the criteria of the umbrella cohort (35). The date of disease onset will be considered as the date of confirmation of the diagnosis and/or the date of initiating antihypertensive therapy.

For those diagnosed with HBP during one of the follow-up visits at INC-ICh, the date of disease onset will be recorded as the date of the visit. Additionally, all participants will be contacted by telephone or by email every 6 months to verify whether they have been diagnosed with HBP and/or if they are taking antihypertensive therapy (see Figure 1).

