#### 3.6.2. Periodontitis

The periodontal evaluation will be done every year in terms of probing pocket depth (PPD) and clinical attachment loss (CAL). Examining 6-site-per-tooth in all natural teeth—except third molars–, measuring the distance from the cemento enamel junction (CEJ) to pocket depth and the distance from the gingival margin to the CEJ will be performed. Participants will be divided into two groups: (1) participants without periodontitis and (2) those with a diagnosis of periodontitis (mild, moderate and severe) based on *Centers for Disease Control and Prevention and American Academy of Periodontology* (CDC/AAP) definition (47), suggested for epidemiological studies by Holtfreter et al. (48). According to a recent agreement among experts from Europe and USA (48) and recent epidemiologic trends, the 2012 CDC/AAP criteria become a consensus approach for epidemiological studies worldwide (49). Furthermore, the 2017 World Workshop on the Classification of Periodontal and Peri-Implant Diseases and Conditions (50), in Appendix B, recommended that *After a long-standing debate on how to provide data to inform surveillance of periodontal disease, a recent multinational effort has suggested standard reporting of periodontal epidemiology surveys. Such efforts are important to provide comparable data across populations*.

Several international research efforts have actually made use of this definition for periodontitis cases. For instance, a recent study (51) that compared CDC/AAP Case Definition and the EFP/AAP Classification concluded that use of the EFP/AAP classification (as a possible new globally accepted classification) to assess periodontitis prevalence, severity and risk factors when conducting epidemiological surveys may not be totally reliable for use in population surveys. Hence the use of CDC/AAP in these studies is deemed more appropriate. Also, a recent systematic review and meta-analysis of the association of periodontitis with hypertension determined the CDC/AAP as a confident case definition of periodontitis (3).

The implementation of this classification improved reporting quality and permitted meaningful comparisons of the prevalence of periodontal diseases across populations in epidemiological studies (48). Indeed, many recent epidemiological studies with diverse populations in different parts of the world have used this classification (52–57), as well as (58–61) and (61–63).

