#### 9.1.2. Longitudinal Analysis

As part of the longitudinal analysis the incidence of each oral variable included in the study in 30-month periods will be evaluated. Similarly the relative risk for each oral variable included will be evaluated according to different variables considered as risk factors (alcoholism, smoking, among others) through bivariate and multivariable analyses, using generalized linear models, logistic regression models, and multinomial regression models.

Starting with the third evaluation (baseline evaluation + first follow-up + second follow-up), trajectories of oral health conditions will be identified. From these variables associated with each one will be identified (gender, marital status, occupational class, age, education, among others). In the same way trajectories will be considered as risk factors for the development of hypertension in the study participants and will be included in neural network models.

For the statistical association analysis, participants will be classified in two groups: Group 1: without periodontitis and Group 2: with periodontitis (including all those participants that according to the CDC/AAP have mild, moderate, or severe periodontitis). For the sake of this association analysis and by following the consensus of the literature (73–75), participants in Group 2 who start periodontal treatment but do not continue with it until remission will be kept in this group and considered with periodontitis. However, a note will be made with details on the type, the extent of their treatment and the effects on their periodontal health, derived from their periodical periodontal evaluation.

This information will be used for a further *a posteriori* analysis. The information about the extent of their periodontal disease (mild, moderate and severe) will be also considered a posteriori. It is worth noticing that *a posteriori cluster analysis*, for instance, Propensity Score evaluation (93, 94) is not unusual in prospective observational studies subject to constraints, as is this case (95–99).

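### The endpoint is 60-month incidence of hypertension, but blood pressure is measured only every 2 years and the text states no month-60 assessment

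*Protocol article*

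**What the plan says.** The horizon is 60 months throughout. A specific goal in section 2.2 is "Identifying if there is any association between the 60-month incidence of hypertension and the baseline salivary and subgingival microbiome", and the first hypothesis in section 2.3 concerns the risk of hypertension "within a 60-month period controlling for: sex, age, smoking, and oral hygiene habits" and social determinants.

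Measured blood pressure runs on a different interval. Section 3.6.1 states "Blood pressure assessment will be performed every 2 years in accordance with the" cited guideline. Section 3.2.1 gives the umbrella cohort the same interval: participants "are recruited to be evaluated every 2 years for a period of 10 years or until they develop hypertension".

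Between visits, section 3.6.1.2 has everyone "contacted by telephone or by email every 6 months to verify whether they have been diagnosed with HBP and/or if they are taking antihypertensive therapy". It also asks anyone diagnosed at another facility to notify the investigators and attend a visit at which the diagnosis is confirmed.

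Onset is dated in two ways in section 3.6.1.2. For cases found at a follow-up visit, "the date of disease onset will be recorded as the date of the visit". For outside diagnoses it is the date of confirmation and/or of starting treatment.

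Other procedures do reach month 60. In section 3.6.2, "The periodontal evaluation will be done every year in terms of probing pocket depth" and attachment loss, and section 3.3.2 places microbiome sampling at baseline and at 60 months.

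**The concern.** Sixty is not a multiple of 24. A 2-yearly schedule started at baseline gives months 0, 24 and 48, then 72, so the last part of the follow-up period has no scheduled measurement of the outcome.

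The 6-monthly contact does not fill that gap. As described, it asks about a diagnosis or treatment already received and involves no blood-pressure reading. Hypertension that nobody has detected by month 60 is therefore analysed as absence of hypertension. Detection in that stretch also depends on how often a participant sees a clinician, which may differ between people with and without periodontitis.

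There is a second consequence. A case found at a visit may have begun at any time since the previous normal assessment, but is recorded as starting on the visit day. Section 9.2.4 lists proportional hazards and Cox models for the microbiome associations, and these would take that date as exact.

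**Working it through.** **1. Visit grid.** Multiples of 24 up to 60 are 0, 24 and 48, which leaves a gap of 60 − 48 = 12 months. This assumes that sub-cohort baseline is also a blood-pressure visit. If visits follow the umbrella cohort's calendar, the last one inside the window lies between just after month 36 (60 − 24) and month 60, so the gap ranges from 0 to just under 24 months between participants. The protocol does not state which applies.

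**2. Reproducing the plan's figure.** Inputs from section 3.3.1: 10% exposed, significance level 0.05, power 90%, incidence 21.5%, relative risk 2.4. Assumptions: 21.5% is the 60-month risk in the exposed, and the test is two-sided.

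- p1 = 0.215; p0 = 0.215 / 2.4 = 0.0896; B = 0.10; overall P = 0.9 × 0.0896 + 0.1 × 0.215 = 0.1021.
- Sample-size formula for logistic regression with a binary covariate: N = [1.96 √(P(1−P)/B) + 1.2816 √(p0(1−p0) + p1(1−p1)(1−B)/B)]² / [(p1−p0)² (1−B)].
- P(1−P)/B = 0.917, and the second root contains 1.6005. N = 864, against 866 stated. Power at 866 is 90.0%.

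This match leaves out the R² = 0.3 adjustment that the section says was made. A different reading also gives 866: 21.5% in the unexposed, odds ratio about 2.36, one-sided, with R² = 0.3. The text does not settle which was used.

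**3. Stopping at month 48.** Under a constant hazard (an assumption), risk48 = 1 − (1 − risk60)^(48/60).

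- Unexposed: 1 − (1 − 0.0896)^0.8 = 0.0723.
- Exposed: 1 − (1 − 0.215)^0.8 = 0.1761.
- Overall: 0.9 × 0.0723 + 0.1 × 0.1761 = 0.0827.
- Share of 60-month cases arising after month 48: 1 − 0.0827 / 0.1021 = 19%.
- Cases among 866: 88.4 by month 60 and 71.6 by month 48, a difference of about 17.

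**4. Power at 866**, solving the same formula for power, by the share of cases after month 48 that outside diagnosis finds (same share in both groups):

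| Share found | Risk unexposed / exposed | Power |
|---|---|---|
| none | 7.2% / 17.6% | 84% |
| half | 8.1% / 19.6% | 87% |
| three quarters | 8.5% / 20.5% | 89% |
| all | 9.0% / 21.5% | 90% |

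**5. Other reading of section 3.3.1.** With 21.5% in the unexposed and an odds ratio of 2.36, p1 = 0.215 × 2.36 / (0.785 + 0.215 × 2.36) = 0.393. The month-48 risks are 17.6% and 32.9%, 18% of cases arise after month 48 (about 36 of 866), and one-sided power with R² = 0.3 falls from 90% to 85% if none is found. The size of the effect hardly depends on the reading.

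**6. Onset date.** A case found at a visit, after a normal assessment 24 months earlier, is dated 0 to 24 months late. If onset is uniform over the interval, the mean delay is 24 / 2 = 12 months.

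**The case against.** The strongest reply is that the schedule may be sounder than the text shows. Months 0, 24 and 48 are written nowhere; they are inferred. Figure 1, which outlines the 60-month follow-up, is not available here and could contain a closing blood-pressure visit. Section 7 mentions blood-pressure cuffs among the infection-control measures, which hints that readings may be taken at the dental site. All this stands, and it rules out the claim that 60-month incidence cannot be measured. It does not remove the mismatch: if a closing visit is planned, section 3.6.1 must be reconciled with it.

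A reader might also infer that onset is known only to within 24 months. That is too strong. The 6-monthly contact and the outside-diagnosis route supply dates for cases detected between visits, although these are dates of confirmation or treatment and not of biological onset.

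Nor does the text pair the month-60 microbiome samples with a month-48 blood-pressure status. It describes the groups by whether hypertension developed.

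The dating error has limited reach. The sample size rests on logistic regression, and section 9.1.2 names generalized linear, logistic and multinomial models; none of these needs an onset date. Cox regression appears as one option in section 9.2.4. Truncation alone also leaves the relative risk almost unchanged (0.1761 / 0.0723 = 2.43 against 2.40), so its main cost is lost events. Bias would require detection after the last visit to differ by exposure.

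The 30-month periods in section 9.1.2 concern oral variables, and retention after dropout is a separate question. Neither is evidence on this point.

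**Conclusion.** The point holds in this form: the stated blood-pressure schedule does not reach the 60-month endpoint, no month-60 assessment is stated, and after the last scheduled measurement only hypertension already diagnosed or treated elsewhere can be found.

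Under a constant hazard and visits starting at baseline, 18% to 19% of 60-month cases fall after month 48 on the two readings that reproduce 866. The drop in power from 90% to about 84% (85% on the second reading) is a worst case for that schedule, not an expected value, because it assumes that none of these cases is found. It should not be read as the study's actual power, since section 3.3.1 states neither which group nor what time span the 21.5% describes. Late dating of visit-detected onset is a real error of up to 24 months, but only for time-to-event analyses.

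This should be corrected. It concerns the dependent variable and is cheap to repair, but it does not invalidate the design.

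**What to change.** 1. State the blood-pressure visit months relative to sub-cohort baseline, and say whether they follow the umbrella cohort's calendar.
2. Then do one of the following:
   - add or confirm a blood-pressure assessment at the month-60 visit, followed by the protocol's existing confirmation steps (sections 3.6.1 and 3.6.1.2) for raised readings; or
   - restate the horizon in the goals, hypotheses and sample size as the last scheduled blood-pressure visit (48 months if visits start at baseline), with the power that follows.
3. In any time-to-event analysis, treat visit-detected onset as interval-censored between the last normal assessment and the visit, for example with a discrete-time complementary log-log model over the visit intervals.

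Cost: the first option is more than a single cuff reading, because those who screen high need the repeat visits and home monitoring that the protocol already requires, and the oral visits and the confirmation of diagnosis take place at different institutions. The second option costs only wording and a somewhat lower stated power. The interval-censored model is standard and needs no extra data.

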##### 3.6.1.1. Office Blood Pressure Measurement Classification (SBP/DBP, mm Hg)

Normal BP, <130 and <85High-normal BP, 130–139 and/or 85–89Grade 1 hypertension, 140–159 and/or 90–99Grade 2 hypertension, ≥160 and/or ≥100

*3.6.1.1.1. Preparation and Position*. Before office BP measurements, participants will be advised to have an empty bladder, not to exercise and not to smoke, drink coffee or tea, for at least 30 min on the visit day. Participants will be seated in a quiet room (neither participant nor staff should talk before, during and between measurements) with comfortable temperature for at least 5 min before the first evaluation, arm resting on table with mid-arm at heart level; back supported on a chair; legs uncrossed and feet flat on the floor (39).

*3.6.1.1.2. Monitoring Schedule*. BP will be measured in the right arm three times with 1 min between them with a validated electronic (oscillometric) upper-arm cuff device (40–42) according to the individual's arm circumference. The average of the last 2 measurements will be calculated. If one of the three measurements is remarkably different, a fourth measurement will be taken. If BP of first reading (first three measurements) is less than 130/85 mm Hg no further measurement is required (39).

